**Figure 2 F2:**
[figure not shown]
Activity flowchart.

### Characterization of the study

2.7

The experimental design will consist of 2 groups: G1-older adults with halitosis (SH2 ≥ 112 ppb) who wear complete dentures and treatment with a tongue scraper (n = 20); G2-older adults with halitosis (SH2 ≥ 112 ppb) who wear complete dentures and treatment with PDT (n = 20). The evaluation of halitosis will be performed at baseline (1st session), after treatment with a tongue scraper or PDT (1st session) and after 1 week (2nd session) (Fig. 3).

**Figure 3 F3:**
[figure not shown]
SPIRIT figure.

### Patient history

2.8

After filling out a conventional questionnaire addressing the patient's general health, data will be collected on demographic (age, sex, marital status, occupation, schooling, living conditions, and income), medical (principal complaint, current state of disease, medical history, dental history, and use of medications), and behavioral (alcohol intake, eating habits, and oral hygiene habits) characteristics.

### Assessment of halitosis

2.9

This is the primary outcome of the study. The portable Oral Chroma^TM^ (Abilit, Japan) will be used for the assessment of halitosis, which is a highly sensitive semiconductor gas sensor. The participant was instructed to rinse with cysteine (10 mM) for 1 minute, with the aim of selecting the gases produced by bacteria degradation. A syringe will be placed in the patient's mouth with the plunger completely inserted and the participant will breathe through the nose with the mouth closed for 1 minute, being careful not to touch the tip of the syringe with the tongue. The plunger will then be withdrawn to fill the chamber with air. This procedure will be repeated. The tip of the syringe will be cleaned to remove the saliva. The gas injection needle will be placed on the syringe and the plunger will be adjusted to 0.5 ml. This air will be injected into the input of the device in a single motion. When connected to a computer, the specific software accompanying Oral Chroma^TM^ produces a graph with peaks and values corresponding to the concentrations of VSCs (from 0 to 1000 ppb) with considerable precision after a period of 8 minutes. The results are stored in both the program and the device. As it is a device, Oral Chroma^TM^ is a blind assessor.

To standardize the readings, the exam will be performed in the morning and the participants will be instructed to avoid the ingestion of some strong spices, onion, garlic, and alcohol as well as the use of an antiseptic mouthwash 48 hours prior to the exam. The participants will also be instructed to abstain from coffee, mints, chewing gum, oral hygiene products, and personal hygiene products with perfume (after shave, deodorant, creams, or tonic) and brush only with water on the day of the test as well as not eat anything at least 2 hours prior to the test.^[23–25]^

*Analysis of Oral Health Impact Profile* (OHIP-14 questionnaire): The OHIP-14 is a shortened version of the original OHIP questionnaire used for the evaluation of the impact of oral health on quality of life. The items are distributed among subscales (functional limitation, pain, psychological discomfort, physical disability, psychological disability, social disability, and social handicap). The OHIP-14 will be administered by a calibrated examiner on the day the patient history is taken (baseline) and 1 week after treatment for halitosis.

### Treatment with tongue scraper on coated tongue

2.10

The patients in the group G1 will receive treatment with tongue scraper. It will be positioned on the posterior third of the dorsum of the tongue in the region of the vallate papillae and pulled with light pressure to the apex of the tongue, following the manufacturer's instructions. This procedure will be performed only once.^[29]^ The participant will then be instructed to rinse with 50 ml of water for 2 seconds and spit.

### Photodynamic therapy for coated tongue

2.11

The patients in the group G2 will receive PDT. Methylene blue (0.005%) (Fórmula e Ação, São Paulo, Brazil) will be applied in sufficient quantity to cover the middle and posterior thirds of the dorsum of the tongue. After 5 minutes, irradiation will be performed with a red (λ = 660 nm) diode laser, operating with an output power of 100 mW, 9 J, radiant exposure of 320 J/cm^2^ and radiance of 3537 mW/cm^2^, using the point method in direct contact with the tongue (MM Optics Twin Laser, São Paulo, SP, Brazil).^[23–25]^ All parameters can be found in Table 1. Six points will be irradiated, with a distance of 1 cm between points (Fig. 4), considering the light spreading halo and effectiveness of PDT.^[24]^

**Table 1 T1:**
[figure not shown]
Dosimetric parameters used in each group.

**Figure 4 F4:**
[figure not shown]
Irradiation spots in the tongue dorsum.

During the application of the laser, both the patient and operator will use protective eyewear. The stained parts of the tongue will then be washed abundantly with saline solution until the complete removal of the dye.

### Cleaning of dentures

2.12

The edentulous patients will be instructed to remove their dentures for cleaning. Sterile gauzes soaked in a 2% chlorhexidine solution will be applied over the entire inner and outer surfaces of the dentures. The mucosa of the edentulous patients will be cleaned with 0.12% chlorhexidine. After cleaning of the mucosa and dentures, patients will rinse with water for 1 minute.

### Statistical analysis

2.13

The Lilliefors test will be used to determine the normality of the data. If normality is demonstrated, analysis of variance (*t* test student, Bioestat 5.3, Pará, Brazil) will be used to compare continuous and dependent variables among G1 and G.2. If non-normal distribution is demonstrated, Mann Whitney test will be used. The baseline data will be compared to the data collected at 1 week follow-up evaluation. A *P*-value < .05 will be considered indicative of statistical significance. The *χ*^2^ test will be used to compare categorical variables among G1 and G2, at baseline and the 1 week evaluation. These data will be expressed as mean ± standard deviation.

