### Calculation of sample size

2.2

To calculate the sample size we established an error *err* = *x*_1_−*x*_2_ where *x*_1_ and *x*_2_ are the mean values of groups G1 and G2, whose variances are 

, respectively. The effect size was calculated by: 
[figure not shown]

If the normal distribution hypothesis is rejected, the sample size should be corrected by approximately 5%.

Observing statistical samples from the reference Mota et al^[14]^; to estimate the mean values and sample variance we obtain the following sample sizes for each group. G1: 18; G2: 18 (Fig. 1).

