### Randomization

2.6

The 40 individuals with complete denture will be randomized in 2 groups: Group A (20 individuals submitted to treatment with a tongue scraper) and Group B (20 individuals submitted to treatment with PDT) (Fig. 2). Opaque envelopes will be identified with sequential numbers (1–40) and will contain pieces of paper with the information of the corresponding experimental group (A or B). Blocked randomization will be performed in blocks of 5 patients (8 blocks for both treatments; example of a block: AABAB). The envelopes will be sealed and kept in numerical order in a safe place until the time of the treatments. The randomization and preparation of the envelopes will be performed by a researcher who will not otherwise participate in the study. Randomization will be performed using Microsoft Excel, version 2013.

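### The G1 versus G2 comparison names no use of baseline H2S or OHIP-14, and a normality pre-test leaves open whether means or ranks are compared

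*Protocol article*

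**What the plan says.** Section 2.13 sets out the analysis in a few sentences. "The Lilliefors test will be used to determine the normality of the data". If normality holds, Student's t test "will be used to compare continuous and dependent variables among G1 and G.2"; otherwise, "If non-normal distribution is demonstrated, Mann Whitney test will be used". No covariate, change score or paired test is named.

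Baseline enters in one further sentence: "The baseline data will be compared to the data collected at 1 week follow-up evaluation". It does not say how, or whether this bears on the comparison between arms. A P-"value < .05 will be considered indicative of statistical significance", with no statement of one or two sides. The section ends by promising means and standard deviations, and gives no summary for the Mann-Whitney branch.

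Section 2.7 measures halitosis in every patient at baseline, after treatment in the first session, and at 1 week. Section 2.9 takes OHIP-14 at baseline and 1 week, and gives the device's output range as 0 to 1000 ppb. Entry requires H2S of at least 112 ppb (sections 2.4 and 2.7).

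On size, section 2.2 reports that "to estimate the mean values and sample variance we obtain the following sample sizes for each group. G1: 18; G2: 18". It adds: "If the normal distribution hypothesis is rejected, the sample size should be corrected by approximately 5" per cent. Section 2.6 states: "The 40 individuals with complete denture will be randomized in 2 groups", 20 in each.

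**The concern.** There are two separate issues.

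First, a baseline reading of the outcome, on the same device, is available for everyone but has no stated role in comparing the arms. If baseline predicts the 1-week value, an unadjusted test leaves that explained variation in the error term. It also leaves any chance baseline difference in the treatment estimate. In a trial of 40 patients this precision is worth having, and the data are already collected.

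Second, the choice between a comparison of means and a comparison of ranks is made after the outcome data are seen, by a normality test in about 20 patients per arm. The two tests address different quantities, so the reported effect is not fixed in advance.

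**Working it through.** **The plan's own figure.** The 18 per arm cannot be rebuilt: the effect size formula is in a figure not shown, and the text gives no means, SDs or power. Solved backwards for a two-sided 5% t test, 18 per arm corresponds to a standardized difference d of 0.961 at 80% power or 1.11 at 90%. The correction for non-normality gives 18 × 1.05 = 18.9, so 19, which is within the 20 planned.

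**Value of baseline, by formula.** Take n = 20 per arm and d = 0.961 (0.9613 unrounded; 80% power is an assumption). The unadjusted t test has noncentrality d√(n/2) = 3.04 on 38 df. ANCOVA reduces the residual SD by √(1 − ρ²), so d becomes d/√(1 − ρ²), on 2n − 3 = 37 df. The correlation ρ is assumed.

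| ρ | d/√(1 − ρ²) | t test | ANCOVA | Gain (points) |
|---|---|---|---|---|
| 0 | 0.961 | 84.2% | 84.1% | −0.1 |
| 0.3 | 1.008 | 84.2% | 87.3% | 3.1 |
| 0.5 | 1.110 | 84.2% | 92.8% | 8.6 |
| 0.7 | 1.346 | 84.2% | 98.6% | 14.4 |

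**The written rule, by simulation.** The settings are all assumed: 20 per arm; log-normal baseline with median parameter 250 ppb, cut below at 112; effect 0.9 log SD; Lilliefors at 5% in each arm, then t or Mann-Whitney; 20,000 trials per setting. Power at log SD 0.8, without zeros:

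| ρ before the cut | ρ among enrolled | Written rule | Mann-Whitney alone | Log ANCOVA |
|---|---|---|---|---|
| 0 | 0.00 | 77.1% | 76.8% | 78.0% |
| 0.3 | 0.24 | 78.8% | 78.5% | 81.6% |
| 0.5 | 0.41 | 81.2% | 80.9% | 88.7% |
| 0.7 | 0.61 | 85.0% | 84.8% | 97.2% |

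Over log SDs of 0.3 to 1.0, the loss from omitting baseline was none at 0, about 3 points at 0.3, 7 to 10 at 0.5 and 11 to 19 at 0.7. The entry cut lowers the correlation in those enrolled, as the second column shows.

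**What the pre-test does.** Type I error of the written rule was 4.9% to 5.7%, and its power was equal to or slightly above that of Mann-Whitney alone. The method it picks does vary: Mann-Whitney was chosen in about 29% of trials at log SD 0.3, 56–59% at 0.5, 86–87% at 0.8 and 94–96% at 1.0. The two tests disagreed on significance in 2–4% of null trials and 7–23% of trials with an effect.

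**Which adjusted analysis.** Zeros are possible on this device. The next table uses the same model at log SD 0.8, with values capped at 1000 ppb and an assumed share of zeros, equal in both arms. It gives power at ρ = 0.3 / 0.5:

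| Zeros | Written rule | Log(x+1) ANCOVA | Log(x+56) ANCOVA | Rank ANCOVA |
|---|---|---|---|---|
| 0% | 78.5 / 80.6 | 81.6 / 87.9 | 80.1 / 86.7 | 79.6 / 85.7 |
| 10% | 59.6 / 62.3 | 27.6 / 28.3 | 57.8 / 62.0 | 58.8 / 63.5 |
| 30% | 28.3 / 28.7 | 11.0 / 10.7 | 30.8 / 31.5 | 26.2 / 27.1 |

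The offset 56 is half the entry threshold. A second model (median 150 ppb, log SD 0.9, log shift 0.6) with only 5% zeros shows the same reversal. At ρ = 0.4 / 0.6 / 0.8 before the cut, power was 50 / 51 / 63% for the written rule, 31 / 31 / 40% for log(x+1) ANCOVA and 52 / 55 / 76% for rank ANCOVA.

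**The case against.** The strongest reply is that the plan is valid as it stands. Randomization protects the unadjusted tests, type I error is close to 5%, and Mann-Whitney copes well with skew and zeros. All of that stands. The point concerns precision and prespecification, not bias.

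A reader might go further in three ways that the documents do not support.

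- **That the Lilliefors step wastes power.** In simulation it did not; the loss comes from omitting baseline. Nor is a loss certain: it is about nil if baseline and follow-up are uncorrelated, and the article gives no correlation.
- **That ANCOVA on log H2S is the obvious replacement.** The stated range starts at 0 ppb. On log(H2S + 1), a zero lies about 5 log units below a reading of 150 (ln 151 = 5.02), so a few zeros dominate the error variance.
- **That baseline is wholly ignored.** Section 2.13 does compare baseline with 1 week. The sentence is ambiguous and may mean a change score. That would not supply the adjustment: a change score has effect d/√(2(1 − ρ)), which at ρ = 0.3 gives 70.7% power against 84.2% for the follow-up value alone.

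A separate analysis plan may exist, but section 2.13 itself fixes the tests and the rule for choosing between them, so the choice is open to comment.

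**Conclusion.** The point holds in this form. The comparison between arms has no stated baseline adjustment, and a data-driven rule decides whether means or ranks are compared. The defect is plain in the text. Its size is not: every median, SD, correlation and share of zeros above is an assumption. Over correlations of 0 to 0.7 the gain from adjustment runs from about nil to roughly 20 points of power at 20 per arm, and the largest gains need a correlation in enrolled patients that the 112 ppb cut makes harder to reach. The pre-test is a prespecification fault with little measurable effect on error rates.

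Rank ANCOVA was about level with or better than the written rule with no zeros or 10% zeros, and 1.6 to 2.1 points below it at 30%. This should be corrected before analysis, but it does not invalidate the trial.

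**What to change.** In section 2.13:

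- Delete the Lilliefors gate and name one primary analysis of 1-week H2S: a linear model of ranked 1-week H2S on treatment and ranked baseline H2S.
- If a log-scale ANCOVA is preferred because it yields a ratio of geometric means, state beforehand how readings of 0 and 1000 ppb are handled, with a rule under which zeros do not dominate. Do not use log(H2S + 1).
- Keep the unadjusted Mann-Whitney test as a sensitivity analysis.
- Analyse 1-week OHIP-14 adjusted for baseline OHIP-14, without a log transform.
- Say what the sentence comparing baseline with 1 week is for, and whether the 5% level is two-sided.

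The cost is a change of wording and software that fits a linear model. No new data are needed. If baseline proves uninformative, the price is one degree of freedom (84.1% against 84.2% power in the formula above).

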**Discussion::**

This protocol will determine the effectiveness of photodynamic therapy regarding the reduction of halitosis in older adults with complete denture.

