### Strategies for obtaining the adequate recruitment of the participants

2.14

The participants will be recruited from the clinics of *Universidade Nove de Julho*. A researcher ([name]) will perform the exam to detect halitosis in a reserved room at the university. Treatment will be performed immediately after the diagnosis. The participants will be counseled with regard to oral health and will receive a set of instructions for performing daily oral hygiene. If they wish to withdraw their consent, there will be no loss for them. It is expected that patients will complete their participants, due to the benefit of halitosis reduction. Data from those who discontinue will not be used for analysis. After 1 week, all patients will be asked to return to *Universidade Nove de Julho* for the reevaluation of halitosis.

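### The baseline-to-1-week comparison cannot show that PDT is effective: the reading that admits a patient is also the baseline, and neither arm is untreated

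*Protocol article*

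**What the plan says.** - **Entry.** Section 2.4 excludes patients with H2S below 112 ppb. Section 2.7 describes the PDT arm as "older adults with halitosis (SH2 ≥ 112 ppb) who wear complete dentures and treatment with PDT (n = 20") and sets the same threshold for the scraper arm.
- **Timing.** Section 2.7 places the baseline reading in the treatment session: "The evaluation of halitosis will be performed at baseline (1st session"). Section 2.14 adds: "Treatment will be performed immediately after the diagnosis".
- **Arms.** Section 2.6 randomises 40 patients to "Group A (20 individuals submitted to treatment with a tongue scraper) and Group B (20 individuals submitted to treatment with PDT"). There is no untreated or sham arm.
- **Co-interventions.** Under section 2.14 all participants receive oral-health counselling and daily hygiene instructions. The abstract adds cleaning of mucosa and dentures if halitosis persists.
- **Analysis.** Section 2.13 names Student's t test, which "will be used to compare continuous and dependent variables among G1 and G.2", with Mann-Whitney as the non-normal alternative and chi-square for categorical variables between the two groups. It also says: "The baseline data will be compared to the data collected at 1 week follow-up evaluation". No test is attached to that sentence.
- **Aim.** The abstract's discussion says: "This protocol will determine the effectiveness of photodynamic therapy regarding the reduction of halitosis". The main Discussion describes the evaluation of PDT as a comparison with the tongue scraper.

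**The concern.** H2S readings vary within a person from one occasion to the next. If patients are admitted because one reading was high, and that reading is then used as baseline, the group's next reading is lower on average even if nothing effective was done. In this trial nothing separates that fall from a PDT effect within the PDT arm. There is no untreated arm, and hygiene counselling and possible denture cleaning also come between the two readings.

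What is at stake is the conclusion. The abstract promises effectiveness in absolute terms, and section 2.13 plans a significance test of change over time. A significant fall in the PDT arm could be reported as fulfilling that promise although selection alone can produce it.

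**Working it through.** **Is the qualifying reading the baseline?** No single sentence says so. But sections 2.4 and 2.7 make 112 ppb the entry condition, section 2.7 puts baseline in session 1, and section 2.14 has treatment follow the diagnosis at once. No second pre-treatment reading is described. The inference is sound.

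**Inputs.** The article gives no figure on this point to reproduce.
- Threshold 112 ppb; n = 20 per arm; significance level .05 (sections 2.7, 2.13).
- Share of people above threshold, q: 15% to 50%. This borrows the prevalence range in the Introduction (15% to more than 50%); applying it to this clinic is an assumption.
- Test-retest correlation of H2S over a week, ρ: not given; assumed 0.5 to 0.9.
- SD of H2S: not given, so results are in population SD units.

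**Expected fall with no treatment effect.** For normal readings selected above the threshold,

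fall = (1 − ρ) × SD × φ(c)/q, with c = z(1 − q).

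- q = 0.15: c = 1.036, φ(c) = 0.2332, φ(c)/q = 1.55.
- q = 0.50: c = 0, φ(c) = 0.3989, φ(c)/q = 0.798.

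For example, q = 0.15 and ρ = 0.5 give 0.5 × 1.55 = 0.78 SD; q = 0.50 and ρ = 0.9 give 0.1 × 0.798 = 0.08 SD.

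**Simulation with no treatment effect, n = 20 per arm.** 'False reduction' means a two-sided paired t test with P < .05 in the direction of a fall; without selection this would occur in 2.5% of trials.

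| q | ρ | Expected fall (SD) | False reduction, paired t | Patients below 112 ppb at 1 week |
|---|---|---|---|---|
| 15% | 0.5 | 0.78 | 96% | 61% |
| 15% | 0.7 | 0.47 | 78% | 48% |
| 15% | 0.9 | 0.16 | 32% | 28% |
| 50% | 0.5 | 0.40 | 45% | 33% |
| 50% | 0.7 | 0.24 | 28% | 25% |
| 50% | 0.9 | 0.08 | 12% | 14% |

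In the same simulations the between-arm t test at 1 week rejected in 4.5% to 5.5% of trials, that is, at its nominal level.

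**Skewed data.** With log-normal H2S (log-SD 0.8, assumed) and the same ranges, mean ppb falls by 3% to 36% and the paired t test shows a false reduction in 6% to 73% of trials.

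**If an independent-groups t test were used on the before-and-after readings.** On unselected data with n = 20 its true size is about 0.8% (ρ = 0.5) or 0.1% (ρ = 0.7) instead of 5%. For a 0.7 SD shift at ρ = 0.5 its power is 61%, against 85% for the paired test. On selected data with no treatment effect it would still show a false reduction in about 0.2% to 94% of trials over the ranges in the table. The choice of test therefore does not remove the artefact, and a correctly paired test detects it more often.

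**The case against.** The strongest reply is that the trial is randomised, the Discussion describes a comparison with the scraper, and nothing in the text says that efficacy will be judged from within-arm P values. Regression to the mean and counselling given to everyone act on both arms alike. An active comparator is a legitimate choice. The size of the artefact rests on assumed values, and the standardised reading conditions in section 2.9 may keep the correlation high. All of this stands. It limits the point to the within-arm comparison, but does not remove it: section 2.13 plans that comparison under the P < .05 rule, and the abstract's aim omits the comparator.

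Three stronger readings are tempting, and the document does not support them.
- *The trial is invalid.* A reader might infer this, but regression to the mean does not bias the randomised contrast, which can show the effect of PDT relative to the scraper.
- *The plan applies independent-groups tests to paired readings and so gets wrong P values.* Section 2.13 ties its tests to G1 versus G2. For the comparison over time it names none, and Student's t also has a paired form. The mismatch is conditional on a use that is not stated. On unselected data that use would be conservative and lose power; it would not in itself create false positives.
- *The baseline chi-square is meaningless because everyone has halitosis.* Section 2.13 does not say that halitosis status is among the categorical variables. Section 2.8 collects sex, marital status and schooling, for which a baseline comparison of the groups is ordinary.

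**Conclusion.** The point holds for the baseline-to-1-week comparison. A fall there cannot be credited to PDT, so it cannot support the abstract's statement on effectiveness. The direction of the artefact follows from selecting on a reading that is not perfectly repeatable. Its size does not follow from the document: roughly 12% to 96% of null trials would show a false reduction by paired t test, given normal readings, 15% to 50% of people above threshold and a correlation of 0.5 to 0.9. A share above 50% or a correlation above 0.9 would make it smaller. These figures cover selection only; counselling and denture cleaning would add to any fall they cause. The repair is worth making before results are seen.

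**What to change.** 1. State in section 2.13 that efficacy conclusions rest only on the randomised comparison of 1-week H2S between G1 and G2, adjusted for baseline H2S (analysis of covariance, on the log scale if the data are skewed).
2. Report within-arm change from baseline descriptively with a 95% confidence interval. If it is tested, use a paired method (paired t or Wilcoxon signed-rank), and attach no efficacy claim.
3. Reword the aim in the abstract as the effect of PDT relative to a tongue scraper.

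The cost is wording only: baseline H2S is already collected, and no visit, patient or procedure is added. The downside is that the report can no longer claim effectiveness of PDT in absolute terms, which this design could not show in any case. Replacing the test with a paired one without steps 1 and 3 would not be enough.
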